### Data management and monitoring

All data will be recorded electronically by the CRCs. All study-related data will be stored on secure servers at KIOM with frequent back-up procedures in place. Data quality will be ensured by conducting automatic validity and range checks during data entry. Both the principal investigators and the KIOM research team can access the final data sets, and all data will be password protected. The independent data monitoring team of KIOM whose members do not participate in this study will be the data monitoring committee. The trial institutions will be monitored by clinical research associates (CRAs) from KIOM while the study is ongoing; the CRAs will be independent of the research team. The CRAs will conduct monitoring visits at each site at least every 2 months after the enrolment of the first participant. They will review the source documents to confirm whether the data reported in the web-based system are complete and accurate.

### Safety and adverse events

All adverse events due to GBH will be reported in detail and participants showing any adverse event will be treated appropriately by doctors. The most common adverse reactions are expected to be skin rash, itching, anorexia, and diarrhoea. Adverse reactions will be reported to the institutional review board (IRB), and serious and unexpected adverse reactions will be reported to the regulatory authorities.

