### Data collection

The following demographic data will be collected on the enrolment date: age, sex, occupation, height, weight, alcohol habit, and smoking status. Blood tests and blood stasis questionnaire evaluation will be conducted and VAS scores for shoulder pain will be assessed during the screening visit. After randomisation, the ankle–brachial pressure index (ABI), brachial–ankle pulse wave velocity (baPWV), oxygen saturation (SpO_2_), total haemoglobin (SpHb), pleth variability index (PVI), oxygen content (SpOC), pulse rate (PR), methaemoglobin (SpMet), perfusion index (PI), blood pressure (BP), body mass index (BMI), and waist circumference (WC) will be assessed (visit 1). Blood tests, blood stasis questionnaire evaluation, and VAS score evaluation will be conducted again during visit 1 in the waiting treatment group since the subjects are required to wait for 8 weeks after randomisation. SpO_2_, SpHb, PVI, SpOC, PR, SpMet, and PI will be measured using an oximeter (Masimo Corp.). Blood tests, blood stasis questionnaire evaluation, and oximeter measurements will be performed and shoulder pain, ABI, baPWV, BP, BMI, and WC will be assessed every 4 weeks after GBH has been received (visits 2 and 3). Furthermore, compliance and adverse events will be assessed every 4 weeks (visit 2 and 3), and patient satisfaction will be evaluated after 8 weeks of intervention (visit 3). At the follow-up visit in the immediate treatment group, blood tests, blood stasis questionnaire evaluation, oximeter measurements, assessment of shoulder pain, and determination of ABI, baPWV, BP, BMI, and WC will be performed (visit 4). The time points of the evaluations are presented in Table 1.

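### Detailed reporting is limited to adverse events attributed to GBH, and the text schedules assessment on treatment, so the waiting group gives no concurrent control rate for weeks 0–8

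*Protocol article*

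**What the plan says.** Two sections of the protocol article deal with adverse events, and they use different scopes.

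- **Safety and adverse events.** Detailed reporting is tied to attribution: "All adverse events due to GBH will be reported in detail". The same sentence has no such limit when it turns to care: "participants showing any adverse event will be treated appropriately by doctors". The route to the ethics board uses the narrower term again: "Adverse reactions will be reported to the institutional review board (IRB".
- **Data collection.** Here there is no causality limit, but the visits are named: "compliance and adverse events will be assessed every 4 weeks (visit 2 and 3". The preceding text places those visits on treatment, because the outcome measures "will be assessed every 4 weeks after GBH has been received (visits 2 and 3".

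Data collection also lists what happens at the two visits outside treatment. For the end of the wait: "Blood tests, blood stasis questionnaire evaluation, and VAS score evaluation will be conducted again during visit 1 in the waiting treatment group". For the post-treatment visit: "At the follow-up visit in the immediate treatment group, blood tests, blood stasis questionnaire evaluation, oximeter measurements, assessment of shoulder pain", and then "determination of ABI, baPWV, BP, BMI, and WC will be performed (visit 4". Neither list includes adverse events.

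Study design gives the immediate group 8 weeks of treatment and then 8 weeks of follow-up. The waiting group has 8 weeks of waiting and then 8 weeks of treatment. Randomisation, allocation, and blinding states that neither researchers nor participants are blinded. The Discussion adds that the waiting group has no follow-up after treatment.

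**The concern.** The design contains one randomised, concurrent, untreated comparison: weeks 0–8. The adverse-event rules do not use it. A reporting rule that depends on attribution to GBH excludes the untreated period by definition, and it rests on a judgement made with the treatment known.

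The article expects skin rash, itching, anorexia and diarrhoea to be the most common reactions, and it gives no background rate for any of them. Without a rate from the waiting group, the reader of the results has only case-by-case attribution to tell drug effect from background. The Discussion says the results will inform the full-scale trial and, depending on what they show, further trials towards an Investigational New Drug application. A biased or uncontrolled adverse-event count would carry forward into that planning.

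Visit 4 matters for a separate reason. The waiting group has no post-treatment follow-up, so the immediate group's visit 4 is the only planned occasion in either group for asking about events that begin after GBH stops.

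**Working it through.** The plan states no safety sample size or rate, so there is no figure to reproduce. The check sets the two sections side by side and then counts planned person-time.

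**Inputs**
- 40 participants, allocated 1:1, so 20 per group (Sample size).
- Two 8-week periods per group (Study design).
- Adverse events assessed at visits 2 and 3, on GBH (Data collection).
- Drop-out allowance of 25% (Sample size). The main count ignores it; a check follows.
- Assumption: the waiting group's visit 1 falls at the end of the wait. The reason given there for repeating its measurements implies this.

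**Scope of the rule**
1. Data collection gathers adverse events of any cause at the named visits.
2. Safety and adverse events limits detailed reporting to those caused by GBH.
3. A participant in the waiting period has taken no GBH, so no event in that period can meet the condition in step 2.
4. The waiting period therefore adds zero events to the detailed reporting, whatever is asked at visit 1. This step does not depend on the content of Table 1.

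**Coverage as the text lists it** (person-weeks = participants × weeks)

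| Weeks | Group | On GBH | Planned | Covered by a listed assessment |
|---|---|---|---|---|
| 0–8 | Immediate | yes | 20 × 8 = 160 | 160 (visits 2 and 3) |
| 0–8 | Waiting | no | 20 × 8 = 160 | 0 |
| 8–16 | Immediate | no | 20 × 8 = 160 | 0 (none listed at visit 4) |
| 8–16 | Waiting | yes | 20 × 8 = 160 | 160 (visits 2 and 3) |

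The total is 4 × 160 = 640 person-weeks. Listed assessment covers 160 + 160 = 320, or 320/640 = 50%, all of it on GBH. Within the randomised 8 weeks it covers 160 of 160 in the immediate group and 0 of 160 in the waiting group.

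**Drop-out check.** With 25% lost, 40 × 0.75 = 30 remain, or 15 per group if losses are even. If all losses came at the start, each cell would be 15 × 8 = 120, and the contrast would become 120 of 120 against 0 of 120. The imbalance is unchanged.

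**What a controlled table could show.** With 20 per group, the two-sided Fisher p-value for 4 events against 0 is 2 × C(20,4)/C(40,4) = 2 × 4,845/91,390 = 0.106. For 5 against 0 it is 2 × C(20,5)/C(40,5) = 2 × 15,504/658,008 = 0.047. Only a large contrast would reach the plan's 0.05 level, so the table would be descriptive.

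**The case against.** The strongest reply is that this is loose wording in a condensed article. Several stronger readings are tempting, and the document does not support them.

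- *That adverse events are assessed at visits 2 and 3 and nowhere else.* The text never says so. It refers the reader to Table 1 for the time points, and the body of that table is not shown. An adverse-event row at visit 1 or visit 4 cannot be ruled out.
- *That the randomised period yields no safety data.* It does: the immediate group's visits 2 and 3 fall in weeks 0–8. What is missing is the concurrent waiting-group rate.
- *That events judged unrelated are never recorded.* Data collection has no causality limit, and care is promised for any adverse event. The limit applies to detailed reporting, not clearly to collection.
- *That half of the person-time is known to be without any safety information.* The 320 person-weeks off GBH are those for which the text lists no adverse-event question. Blood tests are planned at the waiting group's visit 1 and at visit 4, and blood pressure at visit 4. They are planned as outcomes, but they have some safety value.
- *That the expected reactions are frequent without any drug.* The document gives no background rate, so the point does not rest on this.

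It is also fair to say that the stated objectives are shoulder pain and blood lipids, that GBH is already approved for shoulder discomfort, and that 20 per group cannot test a safety difference.

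All of this limits the claim but does not remove it. The causality condition is a rule that the article states, not a detail left to the full protocol. It conflicts in scope with Data collection, and it excludes the waiting period even if Table 1 has a row there.

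**Conclusion.** The point holds in limited form. The two sections disagree on whether all adverse events count or only those attributed to GBH, and the narrower scope governs detailed reporting in an open-label trial. Applied as written, the waiting group supplies no concurrent control rate for weeks 0–8, so no between-group comparison of reported adverse events is possible. The reporting part of this conclusion needs only the wording of the Safety section.

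The coverage figures rest on the visible text, on 20 per group without drop-out, and on visit 1 closing the wait. The gap at visit 4 is the less certain part: the text lists no adverse-event assessment there, but Table 1 might.

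No numerical error in the plan is involved. The plan should be changed because the loss is avoidable at almost no cost. The gain is a descriptive comparison that depends less on unblinded attribution; it is not a powered safety test.

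**What to change.** 1. Reconcile Safety and adverse events with Data collection so that all adverse events are recorded and reported regardless of cause. Hold the causality judgement as a separate field and do not use it as a condition for reporting.
2. Ask the same standard question at the existing visits in both groups: the waiting group's visit 1 (covering the wait), visits 2 and 3, and the immediate group's visit 4. If Table 1 or the full protocol already has these rows, bring the text into line with them.
3. Tabulate weeks 0–8 by randomised group as the concurrent comparison, and label it descriptive given 20 per group. Show events on GBH in the waiting group, and events in the immediate group's follow-up, separately.

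No new visit is needed. The cost is one question at visits already planned, a few changed sentences and slightly more data entry. Recruitment began in June 2019, so for participants already enrolled, the report should state from what date the wider recording applied.

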## Discussion

The aim of this study, as a pilot trial, is to observe the clinical effectiveness of GBH. The study treatment GBH (known as Gyejibongnyeong-Hwan in Korean medicine, Gui-Zhi-Fu-Ling-Wan in traditional Chinese medicine, and Keishibukuryogan in Kampo medicine) is a herbal medicine used to eliminate blood stasis. It consists of five herbs (Cinnamomi ramulus, *W. extensa*, *P. suffruticosa* Andrews, *P. persica*, and *P. lactiflora*) [17, 18]. GBH has been used mainly for treating primary dysmenorrhoea, uterine myoma [19], and climacteric symptoms such as hot flashes [18]. A phase II trial to assess the efficacy of GBH (TU-025) Tsumura & Co (Tokyo, Japan) for hot flash management was conducted in the United States; however, the results did not show significant clinical effectiveness. GBH has also been reported to be effective in the management of metabolic diseases [14]. In South Korea, GBH is one of the most popular herbal medicines for blood stasis management and has been approved as a treatment for shoulder discomfort by the MFDS [13]. Since GBH has not yet been approved for hyperlipidaemia, indices related to blood lipids will be determined as secondary outcomes. Our research team has plans for further clinical trials for Investigational New Drug application, depending on the results of this pilot trial.

The outcomes used to evaluate blood stasis were also designated as study variables for this pilot trial. A blood stasis questionnaire was developed by KIOM, the results of which will be evaluated based on standard guidelines by Korean medical doctors [20]. A questionnaire for blood stasis with metabolic diseases was developed and published recently [21]. This is an abbreviated version of the original questionnaire; the new questionnaire comprises 15 questions (from the original 31 questions) related to metabolic diseases. The 15-item questionnaire will be used at screening, and after registration, blood stasis will be evaluated using the original questionnaire (Appendix: Table 3). Outcomes associated with oximeter measurements and some biomarkers (i.e., resistin, CRP, SAP, and D-dimer) have been used in previous blood stasis studies and will also be measured in this pilot trial to determine whether they are associated with blood stasis. The ABI and baPWV indicate narrowing and stiffening of arteries and are therefore expected to be appropriate for the evaluation of blood stasis [22].

There are some limitations to this pilot study. First, this is an open-label, wait-list controlled trial in which neither the participants nor the clinical practitioners will be blinded. We could have designed a randomised controlled trial using a placebo; however, we decided to administer GBH to both groups. Since the sample size is relatively small, we adopted a wait-list controlled design that would allow the evaluation of GBH effectiveness, without reducing the number of participants receiving GBH. Second, the outcome measures for shoulder pain are only the VAS score and the CRP level, and these may not be enough. However, this study has been designed to minimise the burden of participants and the number of patient-reported outcomes. Furthermore, the blood stasis questionnaire contains pain-related items; therefore, other measurements for shoulder pain were not included in this study, such as the Shoulder Pain and Disability Index (SPADI) and the Disabilities of the Arm, Shoulder and Hand (DASH) questionnaire [23]. Third, a follow-up investigation will not be performed in the waiting group, due to the length of the entire study period and research funds. Fourth, the VAS score, which is the primary outcome, is self-reported, and there may be a measurement bias. Nonetheless, this study is meaningful because the findings of this study will serve as a reference for designing the full-scale randomised controlled trial.

### Trial status

This document is based on version 1.5 (May 31, 2019) of the study protocol. Recruitment started on June 3, 2019, and is expected to complete by March 31, 2020. As of July 2019, five participants had been enrolled in this study and no one has yet completed the study. The trial is ongoing.

## Data Availability

Not applicable.

## Appendix

**Table 2 Tab2:** Original version of the blood stasis questionnaire

Question	None	Mild	Moderate	Severe	Very severe
1. Having dizziness	①	②	③	④	⑤
2. Having central-type palsy	①	②	③	④	⑤
3. Sublingual varicosities	①	②	③	④	⑤
4. Dark purple of palate mucosa	①	②	③	④	⑤
5. Blackish red gingiva	①	②	③	④	⑤
6. Blackish red lips	①	②	③	④	⑤
7. Blackish red tongue	①	②	③	④	⑤
8. Ecchymosis of tongue	①	②	③	④	⑤
9. Dark colouration of periocular region	①	②	③	④	⑤
10. A dark colouration of the face	①	②	③	④	⑤
11. Having chest pain without angina pectoris	①	②	③	④	⑤
12. Side pain	①	②	③	④	⑤
13. Tenderness and resistance of hypochondrium	①	②	③	④	⑤
14. Tenderness and resistance of navel region	①	②	③	④	⑤
15. Lower abdominal pain	①	②	③	④	⑤
16. Tenderness and resistance of ileocecum	①	②	③	④	⑤
17. Tenderness and resistance of sigmoid colon	①	②	③	④	⑤
18. Haemorrhoid	①	②	③	④	⑤
19. Dark stool	①	②	③	④	⑤
20. Having pain due to sprain of ankle, wrist, and spine	①	②	③	④	⑤
21. Having symptoms (pain, bruise) due to contusion or traffic accident	①	②	③	④	⑤
22. Chronic pain in joint/palsies and numbness	①	②	③	④	⑤
23. Stabbing pain	①	②	③	④	⑤
24. Pain at night	①	②	③	④	⑤
25. Ecchymosis of skin	①	②	③	④	⑤
26. Scaly and rough skin	①	②	③	④	⑤
27. Telangiectasia or angioectasia	①	②	③	④	⑤
28. Palmar erythema	①	②	③	④	⑤
29. Bruised easily	①	②	③	④	⑤
30. Angina pectoris	① No		② Yes		
31. Rough pulse	① No		② Yes		

**Table 3 Tab3:** 15-item questionnaire for the diagnosis of blood stasis with metabolic diseases

Question	Response		Score
1. Angina pectoris	No	Yes	3 points
2. Having chest pain without angina pectoris	No	Yes	
3. Blackish red tongue	No	Yes	
4. Ecchymosis of tongue	No	Yes	
5. Stabbing pain	No	Yes	
6. Sublingual varicosities	No	Yes	2 points
7. Dark purple of palate mucosa	No	Yes	
8. Blackish red lips	No	Yes	
9. Blackish red gingiva	No	Yes	
10. Chronic pain in joint/palsies and numbness	No	Yes	
11. Pain at night	No	Yes	
12. Bruised easily	No	Yes	
13. Dark colouration of periocular region	No	Yes	1 point
14. A dark colouration of the face	No	Yes	
15. Scaly and rough skin	No	Yes	

## Abbreviations

ABI: Ankle–brachial pressure index
ANCOVA: Analysis of covariance
baPWV: Brachial–ankle pulse wave velocity
BMI: Body mass index
BP: Blood pressure
CRIS: Clinical Research Information Service
CRP: C-reactive protein
FBG: Fasting blood glucose
GBH: Gyejibongnyeong-Hwan
HCG: Human chorionic gonadotropin
HDL-C: High-density lipoprotein cholesterol
ITT: Intention to treat
KIOM: Korea Institute of Oriental Medicine
LDL-C: Low-density lipoprotein cholesterol
LOCF: Last observation carried forward
MFDS: Ministry of Food and Drug Safety
PI: Perfusion index
PR: Pulse rate
PVI: Pleth variability index
SAP: Serum amyloid P
SpHb: Total haemoglobin
SpMet: Methaemoglobin
SpO_2_: Oxygen saturation
SpOC: Oxygen content
TC: Total cholesterol
TG: Triglyceride
VAS: Visual analogue scale
WC: Waist circumference
